## STUDY SUMMARY

**BACKGROUND:** Sentinel lymph node biopsy (SLNB) is the standard approach for axillary staging in patients with breast cancer worldwide. The evident trend of breast cancer treatment is going towards minimizing axillary surgery, even in presence of involvement of the sentinel lymph node (SLN). In fact, it is well known that removal of lymph nodes is performed with staging purposes and to improve regional control but not with curative intent. Recent data from a prospective randomized trial which compared axillary dissection vs. no further axillary surgery in presence of positive SLN did not show any difference in term of overall and disease-free survival. Moreover, to date the impact of the prognostic information of axillary lymph node status in the decision-making process is less important than in the past as the adjuvant treatment is more and more tailored on the biological features of the disease rather than on the risk of recurrence.

**DESIGN:** this is a prospective randomized controlled trial in which patients with small breast cancer ( $T \leq 2$  cm), with a negative preoperative assessment of the axilla (ultra-sound with FNAC in presence of doubtful findings) will be randomized into two treatment arms:

1. SLNB  $\pm$  axillary dissection
2. No axillary surgical staging

In the arm 1, SLNB will be completed by axillary dissection when 3 or more positive nodes will be found or in presence of extra-nodal invasion. In case of either micrometastases or macrometastases in 1 or 2 SLNs no axillary dissection will be performed.

### PATIENT POPULATION:

- ✓ breast cancer  $\leq 2$  cm, and a clinically negative axilla
- ✓ any age
- ✓ candidates to breast conserving surgery + radiotherapy
- ✓ negative preoperative assessment of the axilla (ultra-sound  $\pm$  FNAC in case one doubtful node is found)

### HYPOTHESIS AND AIM OF THE STUDY:

The hypothesis of this trial are that:

- ✓ avoiding axillary surgery does not worsen the outcome of patients with small breast cancer
- ✓ the absence of the pathological information on the risk of recurrence given by nodal status is not worsening outcome of these patients
- ✓ pre-operative imaging of the axilla can identify patients with clinically relevant nodal burden.

The aims of this prospective randomized study are:

- ✓ to verify whether, in presence of a negative preoperative axillary assessment, SLN can be spared
- ✓ to verify whether, in presence of a negative preoperative axillary assessment, the decision on adjuvant medical treatment can be taken according only to the biology of the tumour without the prognostic information achieved by SLNB on the nodal status
- ✓ to verify whether, in presence of a negative preoperative axillary assessment, the patients' quality of life can be improved by a less invasive surgical procedure.

## **STUDY OBJECTIVES AND SAMPLE SIZE CONSIDERATIONS**

### **Primary endpoint**

The primary endpoint of the study is distant-disease free survival. This endpoint, a proxy of overall survival, will allow to have reliable results in a shorter period of time compared to overall survival.

### **Secondary endpoints**

Secondary endpoints will be the cumulative incidence of distant recurrences, the cumulative incidence of axillary recurrences, the disease free survival (DFS) and the overall survival (OS). Other secondary endpoints are quality of life and evaluation of type of adjuvant treatment administered.

### **Sample size calculation and statistical considerations**

We will consider women who will undergo SLNB as the reference group, and we will test for non-inferiority the group of women not undergoing any treatment in the axilla. For the purpose of sample size calculation, the 5-year DDFS in the reference group is assumed to be 96.5%. Overall, **1560** women (780 per arm) will be enrolled to decide whether the group without treatment of the axilla is no worse than the reference group, given a margin  $\Delta$  of non-inferiority of 2.5% (maximum tolerable 5-years DDFS = 94%). Statistical power and one-sided type I error are set to 80% and 5%, respectively. After 3 years from the start of accrual an interim safety analysis will be performed.

Standard survival analyses and survival analyses with competing events will be performed. Multivariable Cox regression models will be applied to adjust the risk estimates of interest for other variables. The Chi-square test for trend, Chi-square test and the Fisher exact test will be used to evaluate differences in percentages between the two treatment groups, as appropriate. The T-tests will be used to evaluate differences in means for continuous variables.

## **BACKGROUND AND HYPHOTESIS**

### **Introduction**

Sentinel lymph node biopsy (SLNB) is the standard approach for axillary staging in patients with breast cancer worldwide. This procedure allows to achieve the same staging power as axillary lymph node dissection (ALND) with less complications and better quality of life (1). Even if the false-negative risk can be generally quantified in about 6%, the occurrence of overt axillary lymph node metastases after a negative SLNB has been shown to be much lower than expected being 0.9% after a median follow up of 48 months in a cohort of 3548 patients (2).

The evident trend of breast cancer treatment is going towards minimizing axillary surgery, even in presence of involvement of the SLN. Recently it was completed the accrual of a trial launched by the International Breast Cancer Study Group (IBCSG) which explored the significance and the biological impact of micro-metastases in the SLN. In one arm of this prospective randomized controlled trial which enrolled 933 women, patients with micro-metastases in the SLN did not receive any further treatment (neither surgery nor radiotherapy). The results of this trial are under evaluation. Nevertheless, data taken from the Surveillance, Epidemiology and End Results (3) showed that in the U.S. about 40% of more than 5000 patients with micro-metastases in the SLN did not receive ALND despite this latter still represents the standard treatment in this clinical situation. These data clearly underline that physicians and patients understand that an extensive axillary surgery might not be always required even in presence of an involvement of the SLN.

A preliminary analysis carried out in our institute (4) evaluated outcome of 377 patients with micrometastases in the SLN who did not undergo axillary surgery. In this cohort of patients after a median follow up of 5 years OS was 97.3% and the cumulative incidence of axillary recurrence was 1.6%. At the multivariate analysis tumour size larger than 2 cm and high grade were significantly associated with higher risk of axillary recurrence.

Furthermore, Giuliano et al. (5, 6) recently reported the results of the Trial Z0011 designed by the American College Of Surgeons Oncology Group (ACOSOG) which randomized patients with 1-2 positive SLNs to

receive either ALND or no further axillary surgery. The primary endpoint was overall survival. This multicentric trial started in May 1999 and was concluded in December 2004 after enrolling 891 patients. The Data and Safety Monitoring Committee decided to interrupt the trial because of the low number of events observed and because accrual was slower than expected. Median follow up was 6.3 years. The authors showed that in the group of patients with a positive SLNB who did not receive ALND only 4 axillary relapses occurred (0.9%) (5). Overall survival and Disease-free survival were similar between the two groups, in fact 5-year overall survival was 91.8% (95% confidence interval [CI], 89.1%-94.5%) with ALND and 92.5% (95% CI, 90.0%-95.1%) with SLND alone; 5-year disease-free survival was 82.2% (95% CI, 78.3%-86.3%) with ALND and 83.9% (95% CI, 80.2%-87.9%) with SLND alone. The hazard ratio for treatment-related overall survival was 0.79 (90% CI, 0.56-1.11) without adjustment and 0.87 (90% CI, 0.62-1.23) after adjusting for age and adjuvant therapy.

Even though the early interruption of accrual made this study underpowered to completely fulfil the primary endpoint (OS), the clinical relevance of these data is very important and confirm that removal of lymph nodes does not have curative intent as previously pointed out by PRCTs carried out in the pre-SLNB era (7,8, 9). Therefore, axillary surgery in breast cancer is performed with staging purposes and to achieve local control of the disease. Nevertheless, data from Giuliano and from our group (4-6) proved that excellent local control can be achieved without performing axillary clearance even in presence of involvement of the SLN. Moreover, to date the impact of the prognostic information of axillary lymph node status in the decision-making process is less important than in the past as the adjuvant treatment is more and more tailored on the biological features of the disease rather than on the risk of recurrence (10).

Another important point is the clinical meaning of SLN micrometastases. In fact, after SLNB entered in the routine clinical practice, the diagnosis of micrometastases dramatically increased (3) due to an extensive evaluation of the SLN which made easier to find out even a minimal involvement. Moreover the prognostic impact of micrometastes in the SLN seems to be reduced if compared to the role of micrometastases diagnosed in the pre-SLN era (11). In fact, data from our institute (12) showed that the presence of a single micrometastatic lymph node is associated with a higher risk of distant recurrence as compared to node-

negative disease only for patients undergoing ALND for staging purposes but not for patients who underwent SLNB. We therefore concluded that treatment recommendations for systemic therapy should not take into account the presence of a single micrometastatic lymph node identified during complete serial sectioning of sentinel node. Similar data were published by Hansen et al (13) reporting the outcome of patients with micrometastases in the SLN being similar to node negative patients.

Therefore, if the presence of micrometastases in the SLN should not be considered when deciding recommendations for systemic treatment (11) and if even in presence of metastases in the SLN (6) axillary dissection can be spared, the following questions are: do we need to look for minimal nodal involvement? If not, should we try to switch from a surgical staging to an imaging method of staging the axilla able to diagnose a relevant nodal involvement?

Ultra-sound is a simple method of pre-operative assessment which to date has never been routinely used to address this issue. The presence of adipose tissue in the axillary cavity may represent an intrinsic limitation to this type of imaging method. On the other hand, increasing expertise on this specific topic, low costs, absence of radiation exposure and easy applicability also in conjunction with FNAC make Ultra-sound an ideal method to assess the axilla prior to surgery.

### **Hypothesis of the study**

There are several concepts behind this study. First the acknowledgement that imaging is playing a crucial role in the present and in the future of oncology. Secondly, we are convinced that decisions on adjuvant systemic treatment should be taken considering the biology of the disease rather than the risk of recurrence as this attitude reflects an higher probability for the patient to benefit from a certain type of treatment. Finally, a less invasive surgery associated to a more tailored medical approach is aimed at improving patients' quality of life.

The hypothesis of this trial are that:

- ✓ avoiding axillary surgery is not worsening outcome of patients with small breast cancer
- ✓ the absence of the pathological information on the risk of recurrence given by nodal status is not worsening outcome of these patients
- ✓ pre-operative imaging of the axilla can identify patients with clinically relevant nodal burden

## TRIAL OBJECTIVES

The aims of this prospective randomized study are:

- ✓ To verify whether, in presence of a negative preoperative axillary assessment, SLN can be spared,
- ✓ To verify whether, in presence of a negative preoperative axillary assessment, the decision on adjuvant medical treatment can be taken according only to the biology of the tumour without the prognostic information achieved by SLNB on the nodal status,
- ✓ To verify whether, in presence of a negative preoperative axillary assessment, the patients' quality of life can be improved by a less invasive surgical procedure.

### Primary endpoint

This endpoint, a proxy of overall survival, will allow to have reliable results in a shorter period of time compared to overall survival.

### Secondary endpoint

Secondary endpoints will be the cumulative incidence of distant recurrences, the cumulative incidence of axillary recurrences, the disease free survival (DFS) and the overall survival (OS). Other secondary endpoints are quality of life and evaluation of type of adjuvant treatment administered.

## **PATIENT SELECTION**

### **Eligibility criteria**

- breast cancer  $\leq 2$  cm, and a clinically negative axilla
- any age
- candidates to receive breast conserving surgery + radiotherapy
- negative preoperative assessment of the axilla (ultra-sound with or without FNAC in case one doubtful node is found)
- written informed consent must be signed and dated by the patient and the investigator prior to inclusion.
- patients must be accessible for follow-up.

### **Exclusion criteria**

- synchronous distant metastases
- previous malignancy
- bilateral breast cancer
- multicentric or multifocal breast cancer
- previous primary systemic therapy
- pregnancy or breastfeeding
- pre-operative diagnosis (cytology or histology) of axillary lymph node metastases
- pre-operative radiological evidence of multiple involved or suspicious nodes
- patients with psychiatric, addictive, or any disorder, which compromises ability to give informed consent for participation in this study.

## **REGISTRATION AND RANDOMIZATION**

### **Registration procedures**

1. Verify eligibility for registration.
2. Obtain written informed consent signed and dated by the patient and investigator.
3. All screened subjects will be assigned a registration number (a progressive number preceded by a site number) according to defined by coordinator center

### **Information required at registration**

- Verification of eligibility for registration
- Verification that written informed consent has been signed and dated by the patient and the investigator
- Patient's date of birth
- Patient's initials
- Site name

### **Randomization**

Randomization will be performed using the web-based TENALEA randomization service of the IEO:  
<https://it.tenalea.net/ieo/aleastudydef/>.

The local principal investigator or one of his/her collaborator should first apply by the IEO Division of Epidemiology and Biostatistics for a user name and password.

Thereafter, he can access the programme and after signing on-line, he will enter the randomization form and treatment allocation (whether "SLNB" or "no axillary surgical staging") will be assigned.

The link between ID patient number and that of the treatment will be established during allocation. The registration number will be the sole means of identifying a subject.

A confirmation of the randomization will be sent to the local investigators e-mail address.

For a well balanced randomization, institution will be used as stratification factor.

During study possible unbalances between strata will be checked and a correction on stratification will be made if necessary.

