### Information required by randomization program "Tenalea"

- Patient's date of birth
- Patient's initials
- Institution
- UPN (Unique Patient Number) provided by the sponsor

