## 2. BACKGROUND/INTRODUCTION

### 2.1. STUDY DESIGN

Study design: Prospective randomized controlled non-inferiority trial

Number of centres: 18

Number of Countries: 4

Accrual period for the experimental study phase: 5 years (2012-2017)

Additional follow-up years after the last entry: 5 years (until 2022)

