## 5. STATISTICAL METHODOLOGY

### 5.1. GENERAL METHODOLOGY

Frequencies and percentages will be used to describe categorical baseline characteristics, while means and IQR will be used to describe continuous baseline characteristics. Variables with

missing values will be indicated in the table. Variable distributions will be presented separately by treatment group but, since this is a RCT differences, differences between the two groups will not be tested with statistical tests, such as chi-square or T-test.

Final surgical treatment and recommended adjuvant therapy will be presented separately by treatment group, and differences will be tested using the Chi-square test.

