### **5.2. DATA ANALYSIS**

A description of first events, deaths and follow-up time will be provided in Table 2. Frequencies and percentages will be used to describe first events and deaths, while median with IQR will be used to describe follow-up time.

Survival curves will be estimated using the non-parametric Kaplan-Meier method (DDFS, DFS and OS). Differences in survival will be tested using the Log-Rank test, and the p-value of the test will be reported. Cumulative incidence of distant metastases and of axillary recurrences will be calculated in a competing risk framework: events other than distant metastases or axillary recurrences, respectively, will be treated as competing events. Differences in the cumulative incidence between arms will be evaluated by means of the Gray test, and the p-value of the test will be reported. For the analysis of DDFS, DFS and cumulative incidences, only the data on the first event will be used.

We will use multivariable survival models only if substantial differences in the distribution of baseline characteristics are observed. The univariate analysis will be considered as the main analysis in any case. We will possibly use multivariable Cox models if the proportionality assumption is verified. We will possibly use parametric accelerated failure time regression models if the proportionality assumption is not verified; different distributions will be tested, and the most appropriate will be chosen based on the Akaike's information criterion.

To evaluate the primary hypothesis of non-inferiority in DDFS, we will report the p-value for non-inferiority calculated at five years, based on the pre-specified margin of non-inferiority of 2.5%. This means that observations will be right-censored at five years to evaluate the primary hypothesis. With the assumptions specified in the sample size paragraph, non-inferiority is defined as a hazard ratio (HR) of less than 1.74 for no SLNB versus SLNB. Analyses will be performed using SAS software, version 9.4 (SAS Institute Inc., Cary, NC, USA). All tests will be two-sided.

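### The between-arm test of recommended adjuvant therapy and final surgery ignores institution, the only stratification factor the documents name

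*Supplement*

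**What the plan says.** The first protocol version printed in the supplement says, under Randomization: "For a well balanced randomization, institution will be used as stratification factor". It adds: "During study possible unbalances between strata will be checked and a correction on stratification will be made if necessary". No version names any other stratification factor, and none gives a block size or a minimisation rule.

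The latest protocol version does not repeat either sentence. It lists four items that the Tenalea randomisation program needs: date of birth, initials, institution and the sponsor's patient number. Nothing in it withdraws stratification by institution.

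SAP 2.1 gives "Number of centres: 18", in 4 countries. SAP 5.1 says: "Final surgical treatment and recommended adjuvant therapy will be presented separately by treatment group, and differences will be tested using the Chi-square test". SAP 5.2 says: "Differences in survival will be tested using the Log-Rank test, and the p-value of the test will be reported". It plans the Gray test in the same unstratified form and adds: "The univariate analysis will be considered as the main analysis in any case". Adjusted models are survival models only. They are triggered by observed baseline imbalance, and centre is not among the baseline characteristics in SAP 4.3, where it appears only as a supplementary table of counts.

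**The concern.** When allocation is balanced within centres, differences between centres in how often a therapy is recommended cannot contribute to the difference between arms. A plain chi-square test still counts that variation as noise. Its standard error is then too large, so the test rejects less often than its nominal level and is less able to detect a real difference.

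This matters most for recommended adjuvant therapy. The only secondary objective in SAP 1.2 (printed twice) is whether adjuvant decisions can rest on tumour biology without nodal status. Recommended adjuvant therapy is a listed secondary outcome in SAP 4.2, and the chi-square is its only planned between-arm test. Recommendations may plausibly vary across 18 centres in 4 countries, although the documents give no figure. If they do, a real shift in prescribing caused by losing the nodal information is somewhat easier to miss.

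**Working it through.** **The plan's own figures.** The margin as a hazard ratio is ln(0.94)/ln(0.965) = 1.737, which matches the SAP's 1.74. At one-sided 5% and 80% power this needs 4 × (1.645 + 0.842)² / (ln 1.737)² ≈ 81.2 events. With exponential survival, both arms at 96.5%, and 5 + 5 years, the event probability is 0.0520. That gives N of about 1561 to 1562, against the stated 1560. The plan gives no size or power figure for the adjuvant-therapy test.

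**Chi-square test under balance within centre.** Let ρ be the share of outcome variance that lies between centres (the ICC). The true variance of the arm difference is (1 − ρ) times the variance that the plain test uses. So:

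- true size of the plain test = 2[1 − Φ(1.960/√(1 − ρ))]
- power of the plain test, where the usual formula promises 80% = Φ(0.842/√(1 − ρ))
- power of the stratified test at the same effect = Φ(2.802/√(1 − ρ) − 1.960)

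The documents do not give ρ, so it is an assumption shown over a range:

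| ICC | Size, plain | Power, plain | Power, stratified | Gap |
|---|---|---|---|---|
| 0 | 5.0% | 80.0% | 80.0% | 0 |
| 0.02 | 4.8% | 80.2% | 80.8% | 0.6 |
| 0.05 | 4.4% | 80.6% | 82.0% | 1.4 |
| 0.10 | 3.9% | 81.3% | 84.0% | 2.7 |
| 0.20 | 2.8% | 82.7% | 87.9% | 5.2 |

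To translate the ICC, assume 25% use, so the outcome variance is 0.25 × 0.75 = 0.1875. A between-centre SD of 10 points is then an ICC of 0.01/0.1875 ≈ 0.05, and an SD of 20 points is 0.04/0.1875 ≈ 0.21.

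**Check by simulation.** Assumptions: 1560 women, 18 centres of 34 to 342, blocks of 4 within centre, 4000 trials per setting. The Monte Carlo standard error on a 5% rate is √(0.05 × 0.95/4000) ≈ 0.3 points.

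- No centre effect: size 5.35% plain against 5.4% Cochran-Mantel-Haenszel.
- Between-centre logit SD 0.5: size 4.5% against 5.1%; power 82.0% against 83.1%.
- Logit SD 1.0: size 2.9% against 4.2%; power 76.3% against 80.4%.

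**DDFS, censored at 5 years.** The same centres were used, with 2500 trials per setting. At a true within-centre HR of 1.737, the mean unstratified and stratified HRs were 1.739 and 1.741, 1.744 and 1.750, and 1.752 and 1.767, for centre log-hazard SDs of 0.3, 0.5 and 0.8. The rates of declaring non-inferiority were:

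- at the margin: 5.4% and 5.4%, 4.9% and 4.8%, 5.5% and 5.5%
- at a true HR of 1: 65.5% and 65.4%, 63.6% and 63.6%, 62.2% and 62.0%

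The largest difference is 0.2 points.

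Analytically, with gamma frailty of variance θ and H = −ln 0.965 = 0.0356, the marginal HR at 5 years is h(1 + θH)/(1 + θhH). For h = 1.737 this is 1.735 at θ = 0.05, 1.726 at θ = 0.25 and 1.694 at θ = 1.0. At h = 1 it is exactly 1.

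**The case against.** The strongest objection is to the premise. The explicit stratification sentence stands only in a protocol version that appears superseded: its axillary-dissection rule and its faxed forms differ from the latest protocol. An item entered at randomisation is not a declared stratum, and the same version allows the stratification to be corrected during the study. Without restricted allocation within centre, the plain chi-square keeps its nominal size. This stands, and it is why the loss is stated as conditional and why the actual allocation method needs to be written down. It does not remove the point, since no later text withdraws the factor and institution is still supplied to the program.

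Second, the size of the loss rests on assumed between-centre variation. At an ICC of 0.05 or less the power gap is 1.4 points or less, and about 5 points needs an ICC near 0.20, which is extreme. The error is also conservative, so it creates no false positives. This stands too.

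Third, a reader might infer that the unstratified DDFS hazard ratio is biased towards 1 and so favours non-inferiority. The documents do not support that. The 1.74 margin comes from whole-population 5-year rates of 96.5% and 94%, so the unstratified HR is its natural counterpart. A centre-conditional HR lying further from 1 is non-collapsibility, a different estimand and not an error. The decision barely moves in any case.

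A reader might also infer that a non-significant adjuvant-therapy test would be taken as proof that biology alone suffices. The SAP states no such rule.

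**Conclusion.** The point holds as a cheap improvement to a secondary analysis. The SAP's test of recommended adjuvant therapy and final surgery does not use the only stratification factor that the documents name. Two conditions are needed for this to matter: allocation balanced within institution, and prescribing that differs between centres. The documents establish neither. If both hold, the test loses about 0.2 to 2 points of size and 0.6 to 5 points of power for an ICC of 0.02 to 0.20. If there is no centre effect, it loses nothing.

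For DDFS the effect on the non-inferiority decision is negligible, about 0.2 points or less. The planned unstratified analysis should stay the main one, and the primary result is not called into question.

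**What to change.** - In SAP 5.1, replace the chi-square test for recommended adjuvant therapy and final surgery with a Cochran-Mantel-Haenszel test and a stratified risk difference by institution. Pool small centres by a rule fixed before the data are examined.
- In the latest protocol and the SAP, state the allocation method and stratification factor actually used, including any correction made during the study.
- In SAP 5.2, keep the unstratified analyses of DDFS, DFS, OS and the cumulative incidences as main. Add institution-stratified Cox/log-rank and Gray analyses as sensitivity analyses.

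Institution is already recorded for every woman, so the cost is wording and a strata option in each procedure. The only downside is a negligible loss of information from very small centres, which pooling limits.
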